## Abstract

**Background::**

Patients with large defects in the annulus fibrosus following lumbar discectomy have high rates of symptomatic reherniation. The Barricaid annular closure device provides durable occlusion of the annular defect and has been shown to significantly lower the risk of symptomatic reherniation in a large European randomized trial. However, the performance of the Barricaid device in a United States (US) population has not been previously reported.

**Design and methods::**

This is a historically controlled post-market multicenter study to determine the safety and efficacy of the Barricaid device when used in addition to primary lumbar discectomy in a US population. A total of 75 patients with large annular defects will receive the Barricaid device following lumbar discectomy at up to 25 sites in the US and will return for clinical and imaging follow-up at 4 weeks, 3 months, and 1 year. Trial oversight will be provided by a data safety monitoring board and imaging studies will be read by an independent imaging core laboratory. Patients treated with the Barricaid device in a previous European randomized trial with comparable eligibility criteria, surgical procedures, and outcome measures will serve as historical controls. Main outcomes will include back pain severity, leg pain severity, Oswestry Disability Index, health utility on the EuroQol-5 Dimension questionnaire, complications, symptomatic reherniation, and reoperation. Propensity score adjustment using inverse probability of treatment weighting will be used to adjust for differences in baseline patient characteristics between the US trial participants and European historical controls.

**Ethics and dissemination::**

This study was approved by a central institutional review board. The study results of this trial will be widely disseminated at conference proceedings and published in peer-reviewed journals. The outcomes of this study will have important clinical and economic implications for all stakeholders involved in treating patients with lumbar discectomy in the US.

**Study registration::**

ClinicalTrials.gov (https://clinicaltrials.gov): NCT03986580.

**Level of evidence::**

3.

## Introduction

1

Lumbar disc herniation is a localized displacement of disc material beyond the normal margins of the intervertebral disc space^[1]^ and is the primary cause of sciatica, which affects between 1% and 5% of the adult population each year.^[2]^ First-line treatments for sciatica are nonsurgical and may consist of physical therapy, pharmacologic therapy, and/or epidural steroid injection. Regardless of whether conservative treatment is undertaken, acute sciatica symptoms eventually subside in most patients.^[3,4]^ In patients whose symptoms are resistant to conservative treatments, lumbar discectomy may be considered. Surgery typically results in faster symptom relief than continued conservative care^[5]^ and this clinical advantage persists over longer term follow-up.^[1]^ Consequently, lumbar discectomy has emerged as one of the most commonly performed spinal surgeries.^[6]^

Among patients undergoing lumbar discectomy, recurrent disc herniation occurs in 7% to 18% of patients within 2 years.^[7–10]^ Symptomatic reherniation requires reoperation in nearly 80% of cases.^[11]^ Patients at highest risk for reherniation are those with an annular defect of at least 6 mm width at completion of the lumbar discectomy procedure.^[12]^ This high-risk patient population is easily identifiable by measuring the annular defect width with a Penfield probe or specialized measurement tools. Historically, there has been a considerable unmet therapeutic need in this high-risk patient population. Over the last several decades, multiple attempts at the development of techniques and technologies to repair annular defects have been met with limited success.^[13]^

A bone-anchored device intended to occlude large annular defects after lumbar discectomy (Barricaid, Intrinsic Therapeutics, Woburn, MA) received Food and Drug Administration approval in 2019 based, in part, on 2-year safety and efficacy results from a 554-patient randomized trial conducted in Europe.^[14]^ Due to potential regional differences in patient characteristics or surgical practices, it is important to confirm the generalizability of these results to patients in the United States (US). The purpose of this historically controlled post-market confirmatory study is to report the safety and efficacy of the Barricaid annular closure device when used in addition to a primary lumbar discectomy procedure in a US patient population.

## Design and methods

2

The protocol for this study was developed in accordance with the SPIRIT 2013 guidance for protocols of clinical trials.^[15]^

### Study design

2.1

This is a prospective, multicenter, single-arm, historically controlled, confirmatory study that will be performed at up to 25 sites in the US. Patient recruitment is planned to begin in February 2020. The total study duration is expected to be 1.5 years, with 6 months of patient recruitment and 1 year of follow-up. Patient outcomes in this US trial of the Barricaid device (US Barricaid) will be descriptively compared with those from the Barricaid arm of a European randomized controlled trial consisting of 276 patients (EU Barricaid Controls).^[14]^ Propensity score methods will be used to adjust for differences in baseline patient characteristics between the US Barricaid patients and EU Barricaid Controls. The trial was prospectively registered at ClinicalTrials.gov (NCT03986580) before first patient enrollment. Trial oversight will be provided by a data safety monitoring board and data will be routinely monitored for accuracy.

### Participants and eligibility criteria

2.2

Participants will undergo preoperative axial and sagittal magnetic resonance imaging (MRI) of the lumbar spine, low-dose multiplanar computed tomography of the target lumbar level, and 4-view x-rays (standing flexion-extension, lateral, anteroposterior). Key eligibility criteria are lumbar disc herniation at L4–L5 or L5–S1, leg pain severity at least 40 mm on a visual analogue scale of 100 mm length, a score of at least 40 on the Oswestry Disability Index (ODI)^[16]^ despite at least 6 weeks of nonsurgical management, and a positive straight leg raise sign on physical examination. Key exclusion criteria are previous spinal surgery at the herniated level, spondylolisthesis with at least 25% slip at the index level, and lumbar osteoporosis. Patients who meet all preoperative eligibility criteria will undergo limited lumbar discectomy during which the final eligibility criterion regarding annular defect size will be evaluated. A complete list of study eligibility criteria is provided in Table 1.

**Table 1 T1:**
[figure not shown]
Patient eligibility criteria.

### Surgical procedure

2.3

Patients will be treated with limited lumbar microdiscectomy using an interlaminar transflaval approach as described by Spengler.^[17]^ At completion of the limited discectomy procedure, patients will then be assessed for the final eligibility criterion by measuring the size of the annular defect. Patients with a large annular defect, defined as 4 to 6 mm tall and 6 to 10 mm wide, will be enrolled in the trial and treated with the Barricaid device. Patients with annular defect sizes outside of the eligible range will be excluded from further trial participation.

The Barricaid device is a permanent implant that has 2 major subcomponents: a flexible woven polymer fabric component intended to close the annular defect, and a bone anchor to secure the device to an adjacent vertebral body (Fig. 1). The occlusion component consists of a flexible polymer that is designed to prevent reherniation by physically blocking the annulus at the post-surgery defect to maintain hydrostatic pressure inside the nucleus pulposus,^[18]^ and containing a platinum-iridium radiopaque marker to permit radiographic visualization. The anchor component is a saw-toothed titanium alloy that is secured into either the caudal-adjacent or cranial-adjacent vertebral body to resist migration.

**Figure 1 F1:**
[figure not shown]
The Barricaid annular closure device. The device is comprised of a flexible polymer occlusion component that is attached to a titanium bone anchor.

After confirmation of a large annular defect, an alignment trial will be performed under fluoroscopic control to establish the correct position and angle of the Barricaid device. Next, the device will be implanted under fluoroscopic guidance by impacting the anchor into the vertebral body while the occlusion component simultaneously enters the annular defect to prevent expulsion of disc material into the extradiscal space. After fluoroscopic confirmation of correct device placement, the surgical site will be inspected and standard wound closure will be performed.

### Outcomes

2.4

Follow-up visits will occur at 4 weeks, 3 months, and 1 year posttreatment. Magnetic resonance imaging with axial and sagittal images of the lumbar spine, low-dose multiplanar computed tomography of the target level only, and x-rays will be performed during follow-up. Back pain severity, leg pain severity, ODI, EuroQol-5 Dimension (EQ-5D) questionnaire, complications, symptomatic reherniation, and reoperation will be assessed at each follow-up visit. A schedule of patient assessments during the study is provided in Table 2.

**Table 2 T2:**
[figure not shown]
Study assessments at each follow-up interval.

Back and leg pain severity will be separately assessed on a 100 mm visual analogue scale. Back disability will be evaluated with the ODI using a 0 to 100 scale where higher scores represent greater disability. Health utility will be evaluated with the EQ-5D questionnaire.^[19]^ This patient-reported questionnaire consists of 5 domains (mobility, self-care, usual activities, pain/discomfort, and anxiety/depression), each of which can take 1 of 3 responses. Possible responses include 3 levels of severity (no problems/some or moderate problems/extreme problems) within each EQ-5D dimension. The occurrence of adverse events will be evaluated at each visit and adjudicated for seriousness and relation to the procedure or device by an independent data safety monitoring board. Symptomatic reherniation will be defined as: confirmed reherniation during a reoperation, imaging core lab confirmation of reherniation based on MRI performed at an unscheduled visit due to patient symptoms, or imaging core lab confirmation of reherniation based on MRI performed at an scheduled visit in patients with ODI ≥40 and positive leg raise sign, or with an adverse event deemed related to reherniation, lumbar/leg pain, or a neurological event (Fig. 2). Index-level reoperations will be defined as any surgical procedure performed at the level of the original herniation, regardless of side or reason, during follow-up.

**Figure 2 F2:**
[figure not shown]
Algorithm to determine occurrence of symptomatic reherniation. AE = adverse event, HNP = herniated nucleus pulposus, MRI = magnetic resonance imaging, ODI = Oswestry Disability Index, VAS = visual analogue scale.

An independent imaging core laboratory will read imaging to assess device status and anatomical characteristics following the procedure. Key imaging variables will include Modic changes, Pfirrman grade, anterior and posterior ossification, spontaneous fusion, disc degeneration, herniation recurrence, annular tears/fissures, and device events such as device integrity, migration, and subsidence.

The primary endpoint of the study is the incidence of symptomatic reherniation through the 3-month follow-up visit. Secondary endpoints of the study will include symptomatic reherniation, reoperation, back pain severity, leg pain severity, ODI, and adverse events at 3 months and 1-year follow-up.

### Propensity score adjustment

2.5

We anticipate that patients enrolled in the US Barricaid trial may differ from the EU Barricaid Controls with respect to certain baseline characteristics. Therefore, we will prospectively collect clinically relevant baseline variables including age, sex, body mass index, smoking history, level of herniation, average disc height, herniation type, back pain severity, leg pain severity, and ODI. We will also obtain patient-level data from the EU Barricaid Controls for these variables from the study sponsor. We will then calculate propensity scores using binomial logistic regression to estimate the probability that patients would be enrolled in the US Barricaid trial. Propensity score adjustment using inverse probability of treatment weighting (IPTW) will be used to control for potential baseline covariate imbalances between study groups, thereby providing unbiased estimates of average treatment effects. Compared with other methods of propensity score adjustment such as stratification, matching, or covariate adjustment, IPTW is preferable for the analysis of differences in proportions,^[20]^ which coincides with the planned primary endpoint analysis of this trial. We will verify the performance of the propensity score model by comparing the distribution of covariates between study groups before and after propensity score adjustment using the absolute average standardized difference (ASD) statistic. The ASD will be calculated as the difference in means or proportions between study groups divided by the pooled standard deviation. A negligible difference between treatment groups will be defined as an ASD of <0.1.^[21]^

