## Discussion

3

Annular healing following lumbar discectomy occurs slowly, if at all, and ultimately yields biomechanically inferior fibrous tissue with reduced capacity to accommodate tensile force.^[22–24]^ This makes reherniation of disc material likely to occur under lower biomechanical stresses, especially in patients with large post-surgical annular defects. Several strategies to repair, replace, or regenerate the damaged annulus have been evaluated yet none have resulted in a clinically proven strategy to generate appropriate healing and prevent reherniation. It is likely that prior attempts at annulus repair have failed because exterior repairs are not matched to the demands of intradiscal tensile forces.^[25]^ Since the Barricaid device is anchored into an adjacent vertebral body, this may provide for a more durable repair.

The primary goal of this prospective post-market study of the Barricaid annular closure device is to determine whether clinical outcomes with this device in the US are comparable to those observed in a previous randomized trial with the same device in Europe.^[14]^ The design of this study and the conclusions to be drawn will be strengthened by the fact that patient eligibility criteria, surgical technique, device characteristics, and follow-up methodology including imaging and outcome reporting are comparable in the US Barricaid Trial and the EU Barricaid Controls. Further, potential group differences in important patient characteristics will be accounted for using propensity score methods. Thus, this observational study was appropriately designed to control for several important design factors that might have otherwise introduced bias into the results.

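### The listed propensity-score covariates omit annular defect height and width, so an imbalance in defect size within the eligible range is possible and would go unchecked

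*Protocol article*

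**What the plan says.** The Propensity score adjustment section expects the US patients and the European controls to differ at baseline. It introduces its covariates with "we will prospectively collect clinically relevant baseline variables including age, sex"; the full list is "age, sex, body mass index, smoking history, level of herniation, average disc height, herniation type, back pain severity, leg pain severity, and ODI". It then states: "We will also obtain patient-level data from the EU Barricaid Controls for these variables from the study sponsor". A logistic model on these variables gives the weights. Balance is judged by a standardized difference below 0.1, and the weighting is described as "thereby providing unbiased estimates of average treatment effects". The Statistical analysis section makes the weighted comparison the source of the primary results and reports it as a risk difference with a 95% confidence interval, without a hypothesis test.

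On defect size, the Introduction says: "Patients at highest risk for reherniation are those with an annular defect of at least 6 mm width". The Discussion again counts the high-risk US population by defect size. Under Surgical procedure, once the discectomy is finished, "patients will then be assessed for the final eligibility criterion by measuring the size of the annular defect". The eligible range follows: "Patients with a large annular defect, defined as 4 to 6 mm tall and 6 to 10 mm wide, will be enrolled". Only then is the device placed.

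**The concern.** The article gives defect size a central role as a risk factor: it defines the target population and motivates the device. It is recorded before implantation, so it is a legitimate baseline covariate. Yet it is missing from a list that includes age, sex and smoking history.

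If the US and European patients differ in defect size within the eligible range, and if risk rises with size within that range, part of the weighted risk difference would reflect case mix rather than regional performance. The error could go either way. A US cohort with smaller defects would look better than it should, and one with larger defects would look worse. This matters because the Discussion would treat US rates close to the European ones as sufficient evidence that the device works in US patients. The planned balance check gives no protection for a variable that is not obtained for the European group.

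**Working it through.** **1. The plan's own figure.** With 70 evaluable patients and a rate of 3.0%, the event count is 0.03 × 70 = 2.1. The Clopper-Pearson limits from beta quantiles at that fractional count are 0.39% and 10.16%, which reproduces the stated 0.4% to 10.2%. Nothing in this point disputes that figure.

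**2. Is the list closed?** The word *including* leaves it open for US data collection. The next sentence, however, requests European data for the same variables. A variable not obtained for the European patients can enter neither the logistic model nor the balance table. As written, defect size is outside both.

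**3. Does eligibility make adjustment unnecessary?** Only in part.
- Height × width can still run from 4 × 6 = 24 mm² to 6 × 10 = 60 mm², a ratio of 2.5.
- Herniation level (two levels), leg pain (at least 40 mm) and ODI (at least 40) are also restricted by eligibility, and all three are in the list. The article does not otherwise treat restriction as a reason to leave a variable out.
- The Introduction gives possible regional differences in patients or surgical practice as the reason for the study. The defect is measured at the end of the discectomy, so its size could reflect either.

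**4. How large could the distortion be?** The article supplies the 3.0% planning rate, used here as the European risk. All other inputs are assumptions. Split the eligible range into larger and smaller defects. Let RR be the risk ratio of larger to smaller, and let p_EU and p_US be the shares of larger defects.

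- Risk with a smaller defect: r0 = 0.03 / (1 − p_EU + p_EU × RR)
- US risk from case mix alone: r_US = r0 × (1 − p_US + p_US × RR)
- Spurious risk difference: r_US − 0.03

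Example: with RR = 2, p_EU = 0.5 and p_US = 0.6, r0 = 0.03 / 1.5 = 2.0% and r_US = 2.0% × 1.6 = 3.2%, a spurious difference of 0.2 points.

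| RR (assumed) | 50% vs 50% | 50% EU, 60% US | 50% EU, 70% US | 40% EU, 70% US |
|---|---|---|---|---|
| 1.5 | 0.0 | 0.12 | 0.24 | 0.37 |
| 2 | 0.0 | 0.20 | 0.40 | 0.64 |
| 3 | 0.0 | 0.30 | 0.60 | 1.00 |

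Entries are percentage points. If the US share is the smaller one, the sign reverses.

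**5. Scale.** Ignoring the weights, with 3% in both groups and 70 against 276 patients, the 95% half-width of the risk difference is 1.96 × √(0.03 × 0.97/70 + 0.03 × 0.97/276) = 1.96 × 0.0228 ≈ 4.5 points.

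**The case against.** The strongest reply is that defect size is already controlled by restriction. The Introduction's risk statement is about a threshold of 6 mm width, and every enrolled US patient meets it. The Discussion adds that "patient eligibility criteria, surgical technique, device characteristics, and follow-up methodology including imaging and outcome reporting are comparable" across the two studies. The threshold statement also concerns discectomy patients in general, whereas both cohorts here receive a device meant to occlude the defect. The article does not say that width still predicts reherniation after occlusion. Its one risk model in implanted patients, the 15-variable Cox model in the Discussion, did not include defect size and so is silent either way.

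This stands against a stronger reading that a reader might infer, namely that the adjusted comparison is in fact confounded by defect size. That would need both a risk gradient within 6–10 mm by 4–6 mm and a difference between cohorts within that range. The documents show neither. The reply does not remove the point, because comparable criteria do not ensure equal distributions within them, and the section itself expects baseline differences despite them.

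Three further objections have some force. The list is not strictly closed, although the European data request ties it to the named set. The comparison is descriptive, so no pass/fail decision hangs on a bias of this size; but a wide interval does not remove bias. And nothing states that the European data hold defect size in millimetres. That is an inference from the comparable eligibility criteria.

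**Conclusion.** The point holds as a possible, unchecked imbalance, not as demonstrated confounding. The listed covariates leave out a pre-implant variable by which the article itself defines high risk, and the planned balance check could pass while that variable differs between cohorts. The claim of unbiased estimates therefore goes further than the list supports. The distortion is zero if the two distributions match, and about 0.1 to 1.0 percentage point on a 3% rate under the assumed risk ratios of 1.5 to 3 and the assumed imbalances. The article gives no data to narrow this. It is small beside an unweighted half-width of about 4.5 points. This is a cheap improvement to the primary adjusted analysis, not a flaw that invalidates it.

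**What to change.** - Add intraoperative defect width and height to the covariate list, the European data request, the propensity model and the standardized-difference table.
- If the European data do not hold them as continuous values, use the form in which they were recorded. If they cannot be obtained in usable form or balanced, report this, with any imbalance seen, as a limitation.
- Replace the statement that weighting yields unbiased estimates with one that says the estimates are adjusted for measured covariates.

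Cost: one extended data request and a few words of text. The US measurements are already taken for eligibility. The statistical price is two more terms. Counting one term per variable, the model goes from 75/10 = 7.5 to 75/12 ≈ 6.3 US patients per term, which may slightly increase the variability of the weights. No stated sample size or interval changes.

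### Section 2.5 calls the weighted US–European comparison unbiased for a treatment effect, although both groups receive the same device and region and period coincide with study membership

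*Protocol article*

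**What the plan says.** Section 2.5 (Propensity score adjustment) plans a logistic model to "estimate the probability that patients would be enrolled in the US Barricaid trial". Its named covariates are "age, sex, body mass index, smoking history, level of herniation, average disc height, herniation type, back pain severity, leg pain severity, and ODI". The resulting weights are said to control baseline imbalance between the groups, "thereby providing unbiased estimates of average treatment effects". No condition is attached. Performance is judged by whether the standardized difference of each covariate falls below 0.1.

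The comparator in Section 2.1 (Study design) is the "Barricaid arm of a European randomized controlled trial consisting of 276 patients (EU Barricaid Controls"). The Discussion gives the aim as learning whether US outcomes are "comparable to those observed in a previous randomized trial with the same device in Europe".

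Section 2.6 (Statistical analysis) takes the primary results from the propensity-adjusted comparison. The 3-month reherniation risk difference is reported with a 95% confidence interval and without a hypothesis test.

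The Introduction gives as the reason for the study: "Due to potential regional differences in patient characteristics or surgical practices". The Discussion concludes that the study was "appropriately designed to control for several important design factors that might have otherwise introduced bias into the results". Its last paragraph says that US recurrence rates close to the European ones would be enough to show that the device prevents reherniation in US patients.

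**The concern.** Weighting estimates an average treatment effect only if there is a treatment contrast, no unmeasured confounding, overlap between the groups and a correctly specified score. Even then, weights from an estimated score give consistency, not exact unbiasedness. Here the first condition fails because the device is the same on both sides. The second is not stated and is in doubt on the article's own account of regional practice.

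The label matters because it is attached to the primary result. A small adjusted difference could be taken as clean evidence that the device performs the same in the US, and a larger one as a device or patient effect. Either could partly reflect where, when and how the patients were treated. The planned confidence interval covers sampling error only.

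**Working it through.** **The plan's own figure.** The only precision figure is the 95% interval of 0.4% to 10.2% at a 3.0% rate with 70 evaluable patients. The Clopper-Pearson limits are the 2.5% quantile of Beta(x, n − x + 1) and the 97.5% quantile of Beta(x + 1, n − x). With x = 0.03 × 70 = 2.1 and n = 70 they are 0.39% and 10.16%, which reproduces it. With a whole count, 2/70, they are 0.35% and 9.94%. The figure concerns the US rate alone and is unaffected by this point.

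**What the contrast is.**
- Device: Barricaid in both groups (Section 2.1, Discussion). There is no treatment contrast.
- Modelled outcome of the score: enrolment in the US study (Section 2.5). The exposure is study membership.
- Region: US or Europe, fixed by study.
- Period: US recruitment from February 2020 (Section 2.1). The European 2-year results supported a 2019 approval (Introduction), so those operations date from about 2019 − 2 = 2017 or before. The periods do not overlap.
- Surgical practice: named in the Introduction as a possible regional difference. All ten named covariates describe the patient or the disc. The list is introduced as open, but no patient variable added to it could separate region or period from study membership.

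**Which readings could save the phrase?**
- Effect of the device: not estimable, because nobody in the comparison is without it.
- US use against European use: a legitimate target, but practice is then part of the contrast and treatment effect is the wrong name.
- Device performance with all else equal: needs region, period and practice to have no effect, which is neither stated nor checked.

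The phrase fails under each.

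**What the balance check can miss (illustration; the inputs are assumptions).** Take one unlisted binary factor U, independent of the covariates, with prevalence p_US and p_EU and risk ratio RR. Assume a European risk of 3% and no effect of study membership itself. The risk without U is b = 0.03 / [1 + p_EU(RR − 1)], the US risk is b[1 + p_US(RR − 1)], and the apparent difference is the US risk minus 0.03. For RR = 2, 60% against 30%: b = 0.03/1.3 = 0.02308, US risk = 0.02308 × 1.6 = 0.03692, difference +0.69 points.

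| RR | 50% vs 40% | 60% vs 30% | 80% vs 20% |
|---|---|---|---|
| 1.5 | +0.13 | +0.39 | +0.82 |
| 2 | +0.21 | +0.69 | +1.50 |
| 3 | +0.33 | +1.13 | +2.57 |

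(Percentage points, US minus EU. A factor commoner in Europe would reverse the sign.)

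A simulation with ten measured covariates, a logistic propensity score and a U that doubles the odds of reherniation (risk about 3%, about 351,000 patients per run, 10 runs each) gave:

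| U in US vs EU | Unweighted difference | Weighted difference |
|---|---|---|
| 50% vs 50% | +0.44 | 0.00 |
| 68% vs 45% | +0.92 | +0.48 |
| 81% vs 39% | +1.27 | +0.88 |

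The largest standardized difference on any measured covariate after weighting was about 0.003, far inside the 0.1 limit. Weighting removes what the measured covariates contribute and leaves the rest, and the check passes either way.

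**The case against.** The best defence is that the comparison is descriptive. No hypothesis is tested, unadjusted results are planned as a sensitivity analysis, the article grades its evidence at level 3, and the Discussion calls the study observational and claims control of several factors, not all. It also describes eligibility, technique, device and follow-up methods as comparable. If the question is how the device does in US hands, US practice belongs to the answer and is not a confounder. All of this stands, and it limits the point to one of wording. It does not rescue the phrase: being descriptive removes the test but not the claimed property, comparability is asserted while the Introduction treats practice differences as possible, and a US-against-Europe contrast is not a treatment effect. Nor is this a detail left to a fuller document, since the claim is made outright.

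Stronger readings are tempting and should be resisted:

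- **An experience gap.** Given the 2019 approval and "confirmatory study that will be performed at up to 25 sites in the US. Patient recruitment is planned to begin in February 2020", a reader might infer that US surgeons were less practised. But 75/25 = 3 implants per site is a US-only average, and a minimum because 25 is an upper limit on sites. The article gives no European counterpart and nothing on training. Surgeon experience and concomitant care may differ; the document does not show that they do.
- **Experience that cannot be separated from study.** Only region and period are fixed by study. Experience varies within a study and can be recorded.
- **A demonstrated bias of known size.** No figure in the document gives one. The tables above illustrate a mechanism.
- **A need for added analyses.** About 0.03 × 70 = 2.1 US events are expected, too few to split by implant order. A tipping-point analysis would have no margin or decision rule to tip.

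**Conclusion.** The claim is wrong as written. The primary adjusted risk difference is a between-study difference, US minus European device arm, adjusted for measured baseline characteristics. It is not an average treatment effect, and the plan gives no assurance that it is unbiased. This rests on three things in the document: the same device in both groups, a score for study membership, and region and period that coincide with it. It does not depend on the illustrative range of +0.13 to +2.57 points, which assumes a 3% European risk and invented values for a single unlisted factor.

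The consequence is moderate. The interval of 0.4% to 10.2%, the sample size of 75 and the planned calculations are unchanged. What narrows is the conclusion: a US rate close to the European one describes similarity between two treated cohorts and is not unbiased evidence of a device effect.

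**What to change.** In Section 2.5, replace the claim of unbiased treatment effects with: *between-study (US minus EU) difference adjusted for the listed baseline characteristics; it may also reflect region, period, surgical practice and other unmeasured factors*.

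Make two matching changes in the Discussion. Where it says the design controls for sources of bias, limit this to the measured patient characteristics and name the unmeasured factors as a limitation. In the last paragraph, present agreement with the European rate as similarity of outcomes between two cohorts treated with the device, not as sufficient evidence of efficacy in US patients.

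This is text only, with no added data collection, analysis or patients. The downside is a more modest claim.
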